# Efficacy and safety of polysaccharide iron complex capsules compared with iron sucrose in hemodialysis patients: study protocol for a randomized, open-label, positive control, multicenter trial (IHOPE)

**DOI:** 10.1186/s13063-021-05663-1

**Published:** 2021-10-10

**Keywords:** Kidney failure, Hemodialysis, Anemia, Oral iron, Multicenter, Efficacy and safety

## Abstract

**Background:**

Anemia is one of the main complications of chronic kidney disease especially kidney failure, which includes treatment with erythropoiesis-stimulating agents and iron supplementation, including intravenous and oral iron. However, intravenous iron may pose limitations, such as potential infusion reactions. Oral iron is mainly composed of divalent iron, which can excessively stimulate the gastrointestinal tract. Iron polysaccharide complex capsules are a novel oral iron trivalent supplement with higher iron content and lower gastrointestinal irritation. However, since high-quality evidence-based medicinal support is lacking, it is necessary to conduct clinical studies to further evaluate the effectiveness and safety of oral iron polysaccharide complex in chronic kidney disease patients.

**Methods:**

This randomized controlled trial uses an open-label, parallel group design, where the efficacy and safety of maintenance hemodialysis (MHD) participants is evaluated. The experimental group is assigned erythropoietins and iron polysaccharide complex (two capsules each time, bid), and the control group is assigned erythropoietin and sucrose iron (100mg, 2w) injection. Participants (aged 18–75 years) undergoing maintenance hemodialysis were considered for screening. Inclusion criteria included hemoglobin (Hb) ≥110g/L and < 130g/L, transferrin saturation (TSAT) > 20% and < 50%, and serum ferritin (SF) > 200μg/L and < 500μg/L. Exclusion criteria included acute or chronic bleeding, serum albumin < 35g/L, hypersensitive C-reactive protein (HsCRP) > 10 mg/L, and severe secondary hyperparathyroidism (iPTH ≥ 800 pg/mL). Full inclusion and exclusion criteria are described in the “Methods” section. The primary endpoint is TSAT of the participants at week 12. Secondary endpoints include Hb, SF, hematocrit (Hct), HsCRP, pharmacoeconomic evaluation, drug costs, quality of life, and indicators of oxidative stress. The treatment will last for 24 weeks with a follow-up visit at baseline (within 7 days prior to initial treatment) and weeks 4, 8, 12, 16, 20, and 24 after initial treatment. This clinical research includes 9 hemodialysis centers in mainland China and plans to enroll 186 participants.

**Discussion:**

It is expected that it will provide strong evidence to reveal the clinical efficacy and safety of oral iron in the treatment of chronic CKD-related anemia in MHD patients through this clinical trial.

**Trial registration:**

Chinese Clinical Trial Registry ChiCTR2000031166. Registered on March 23, 2020

## Background

Kidney disease is a serious threat to the health of people globally. Seventy-nine percent of patients in China Dialysis Outcomes and Practice Patterns Study (DOPPS) had Hb < 12 g/dL, compared with 93% in Japan and 70% in North America [1]. According to the latest epidemiological data published in *The Lancet* in 2019, the prevalence of chronic kidney disease (CKD) among Chinese adults is 10.8% [2]. Anemia is one of the major complications in patients with chronic kidney disease, especially those with kidney failure undergoing maintenance dialysis. The incidence of anemia was 51.5% in 2420 participants with CKD as seen in results from a Chinese cross-sectional epidemiological study, published in 2016 [3]. The study showed a high rate of iron deficiency anemia in Chinese patients with CKD, and the degree of iron deficiency was relatively serious [3]. According to a survey conducted for CKD, the incidence of iron deficiency anemia after dialysis was more than 60% [4]. However, iron deficiency anemia is associated with reduced quality of life and an increased risk of cardiovascular disease, which seriously affects the physical and mental health of patients [5]. Several evidence-based data show that iron deficiency anemia results in poor prognosis in patients with kidney failure, and it is associated with the high rates of hospitalization and mortality in patients with kidney failure [6]. There are nearly 800,000 dialysis participants in China, and standardized CKD-related anemia treatment is imperative to slow down exacerbation of complications in patients with CKD post-dialysis. The diagnosis and treatment of CKD-related anemia have shaped clinical practice guidelines [7].

Iron supplementation is an important management strategy for CKD-related anemia. The 2020 edition of Chinese Medical Doctor Association guidelines recommends that hemoglobin levels and iron metabolism status should be identified first and addressed with potential causes of iron deficiency, before starting iron therapy [7]. Whether or not they are treated with recombinant human erythropoietin (EPO), patients with absolute iron deficiency should be treated with iron supplements. Also, patients with functional iron deficiency should be treated with iron supplements after weighing the benefits and risks of treatment. Commonly used iron agents are intravenous iron and oral iron. However, iron overload still exists in clinical intravenous iron therapy. Iron overload further causes increased levels of oxygen free radicals and increased oxidative stress. In 2011, the Japanese Society for Dialysis first warned about the potential toxicity of intravenous iron maintenance therapy [8]. The issue of iron overload continues to be addressed in several guidelines around the world [9]. Moreover, oxidative stress caused by intravenous iron is also a concern for nephrologists. Oral iron reduces the risk of iron overload and has little effect on oxidative stress, but the first and second generations of oral iron have obvious gastrointestinal side effects. Polysaccharide iron complex capsule is the third generation of oral iron agent that has been widely used in clinical practice due to its advantages of little or no stimulation of the gastrointestinal tract, few side effects, stable coordination, good solubility, and high iron content.

Although the PIVOTAL trial [10] has demonstrated the safety of relatively high levels of ferritin and TSAT with IV iron, iron therapy is still a challenge in the clinical treatment of CKD-related anemia; hence, it is necessary to conduct clinical studies to explore the optimal treatment of CKD-related anemia [7–9]. This study is the first multicenter clinical study of iron polysaccharide complex in CKD participants with maintenance hemodialysis. It aims to evaluate the clinical efficacy and safety of oral iron and to provide additional drug options in the treatment of anemia in CKD participants. This study will offer treatment alternatives for people on maintenance dialysis, especially home therapies such as peritoneal dialysis or home hemodialysis, in whom IV iron is inconvenient.

This clinical trial drug iron polysaccharide complex, produced by SPH Qingdao Growful Pharmaceutical Co. Ltd, has been approved by the CFDA (national medicine permission number H20030033) and is a new oral iron supplement.

## Methods

### Objective

The objective of this study is to compare the efficacy of oral iron polysaccharide complex and intravenous ferric sucrose infusion in maintenance hemodialysis participants with corrected anemia and to evaluate the safety and cost-effectiveness ratio of the two treatment regimens.

### Trial design

This study is a multicenter, parallel controlled, randomized, open clinical trial (version 1.1; date 11 Dec. 2019, phase IV post-marketing) in China, which has been registered with the Chinese Clinical Trial Registry (http://www.chictr.org.cn/index.aspx) on March 23, 2020. The trial registration number is ChiCTR2000031166. The detailed flowchart is shown in Fig. 1. All eligible participants will be randomly divided into two groups in a 1:1 ratio: experimental group [conventional drug (erythropoietin) therapy+ iron polysaccharide complex] and control group [conventional drug (erythropoietin) therapy + iron sucrose injection]. Participants will complete the study visit at baseline (within 7 days before the first treatment) and weeks 4, 8, 12, 16, 20, and 24 after the first treatment. We used the SPIRIT reporting guidelines [11] in the current study.

**Fig. 1 Fig1:**
[figure not shown]
Flowchart of the test scheme. Experimental group [conventional drug (erythropoietin) therapy+ iron polysaccharide complex], control group [conventional drug (erythropoietin) therapy + iron sucrose injection]. Primary outcome: TSAT 12 weeks after treatment. Secondary outcomes: iron metabolism, oxidative stress, safety evaluation, pharmacoeconomic evaluation, quality of life score, etc.

### Sample size

This clinical trial set has a non-inferiority threshold of 7 (%) and a variance of 11 (%) for the positive control group. We predict a 2% real difference between the tested drug and positive control in transferrin saturation. The unilateral significance level is 2.5%, with an assurance of 80%. In the case of a 1:1 sample size between the control group and the experimental group, a total of 154 samples will be collected (77 of which will be in the control group and the experimental group, respectively). Considering a 20% drop-out rate, the actual planned inclusion number will be 186 cases.

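### Enrolling 186 does not cover a 20% drop-out (about 149 remain, not 154), and the stated variance of 11 reproduces the sample size only if it is a standard deviation

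*Protocol article*

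**What the plan says.** All the inputs stand in the Sample size section of the protocol article. The trial is a non-inferiority comparison of TSAT, with week 12 as the primary time point (Primary endpoint).

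- Margin: "This clinical trial set has a non-inferiority threshold of 7" (per cent).
- Variability: "a variance of 11 (%) for the positive control group".
- Assumed true difference: "We predict a 2% real difference between the tested drug and positive control in transferrin saturation". No direction is given.
- Error rates: "The unilateral significance level is 2.5" per cent, "with an assurance of 80" per cent.
- Result: "a total of 154 samples will be collected", 77 in each arm.
- Allowance for loss: "Considering a 20% drop-out rate, the actual planned inclusion number will be 186 cases".

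The Abstract and the Setting and recruitment section repeat the 186. Nowhere does the article give a second drop-out rate, another definition of the inflation, or a separate standard deviation.

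**The concern.** A drop-out rate is the share of those enrolled who are lost. To end with 154 after losing 20%, the 154 has to be divided by 0.8; raising it by 20% is not enough. The figure 186 looks like the second operation. If so, the trial falls short of its own evaluable target at exactly the drop-out rate it plans for.

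Separately, a variance of 11 implies a standard deviation of about 3.3 points. Against a margin of 7, that should give a far smaller trial than 154. The unsigned 2-point difference matters too, because in a non-inferiority calculation it either shortens or lengthens the distance to the margin.

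At stake is the trial's only power statement, which concerns the primary endpoint: whether 80% is delivered under the plan's own assumptions, and whether a reader can reproduce the size from the printed inputs.

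**Working it through.** **Inputs (Sample size section).** Margin 7; variability 11; true difference 2; one-sided alpha 0.025 (z = 1.960); power 80% (z = 0.842); allocation 1:1; evaluable 154; drop-out 20%; enrolled 186.

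**Step 1: reproduce 77 per arm.** Take 11 as a standard deviation and the 2 points as against the test drug, so that the distance to the margin is 7 − 2 = 5.

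n per arm = 2 × (1.960 + 0.842)² × 11² / 5² = 75.98, so 76 per arm by the normal approximation. With the noncentral t distribution, 76 per arm gives 79.5% power and 77 per arm gives 80.03%. The stated 77 per arm (154) is therefore reproduced exactly by the t calculation.

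**Step 2: other readings of the same inputs.**

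| Reading | n per arm, normal (unrounded) | n per arm, t |
|---|---|---|
| SD 11, test drug 2 points worse (distance 5) | 75.98 | 77 |
| Variance 11 (SD 3.317), test drug 2 points worse (distance 5) | 6.9 | 8 |
| SD 11, test drug 2 points better (distance 9) | 23.4 | 25 |

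Only the first row gives 77. With a literal variance of 11, 77 per arm would have power above 99.99%. The variance behind 154 is 11² = 121.

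**Step 3: the drop-out allowance.**

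- How 186 arises: 77 × 1.2 = 92.4, rounded up to 93 per arm; 2 × 93 = 186.
- What 20% loss requires: 77 / 0.8 = 96.25, rounded up to 97 per arm; 2 × 97 = 194. Without forcing equal arms, 154 / 0.8 = 192.5, so 193.
- What 186 leaves after 20% loss: 186 × 0.80 = 148.8, or 74.4 per arm.
- Highest drop-out at which 186 still leaves 154: 1 − 154/186 = 17.2%.

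**Step 4: power at what remains (SD 11, distance 5, one-sided 0.025).**

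| Evaluable | Power, t | Power, normal |
|---|---|---|
| 77 + 77 | 80.0% | 80.5% |
| 75 + 74 | 78.7% | 79.2% |
| 74 + 74 | 78.4% | 79.0% |

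**The case against.** The arithmetic is not in dispute; the case on the other side is about weight.

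- **The loss of power is small.** It is about 1.3 to 1.6 points by the t calculation, from a shortfall of about 5 evaluable participants (3 if the normal formula's 152 is taken as the target). Uncertainty about the standard deviation could plausibly move power more than that. This stands, and it limits how serious the point is.
- **The 20% may not all be lost by week 12.** The primary endpoint is at week 12, but follow-up runs to week 24, and the section does not say which period the rate covers. If, as an assumption, loss were even over 24 weeks, about 10% would be lost by week 12. That leaves 186 × 0.90 = 167.4 and t-based power of about 83%. So the power figure has to be conditional on 20% lacking a week-12 TSAT. It does not rescue the text, which ties 154, 20% and 186 together without that distinction.
- **The main analysis set is intention-to-treat with nobody excluded** (Data set category). That keeps participants in the set, but it does not supply a missing week-12 value.
- **The variance is a labelling slip.** The per cent sign already places the 11 on the TSAT scale, and 154 is unaffected. True, but the word is still wrong.
- **An adverse difference is the usual reading in a non-inferiority calculation.** This is fair. The missing sign alone would be only an absent detail, and the finding does not rest on it.

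**Conclusion.** The concern holds. Enrolling 186 with 20% drop-out leaves about 149 evaluable participants, not 154. The plan is 8 short of a correct equal-arm inflation (7 short if the arms need not be equal) and meets its target only up to 17.2% drop-out. Power at 20% loss is about 78.5% by the t calculation, against the stated 80%. That figure assumes a standard deviation of 11, a true difference of 2 points against the oral drug, and that the whole 20% lack a week-12 TSAT.

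The stated variance of 11 is mislabelled. The protocol's own 77 per arm follows only when 11 is used as a standard deviation; taken as a variance, it gives about a tenth of the stated size. The 154 itself is sound on that corrected reading.

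This should be corrected, but it does not threaten the trial's ability to answer its question.

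**What to change.** Leave enrolment at 186 and correct the Sample size paragraph in three places:

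1. **Drop-out.** State that 186 enrolled gives 154 evaluable at up to 17% drop-out. Add that if 20% have no week-12 TSAT, about 149 are evaluable and power is about 78.5%. Name the two-sample t calculation as the basis.
2. **Variability.** Replace the word variance with a standard deviation of 11 percentage points.
3. **Direction.** State that the assumed 2-point difference favours iron sucrose, leaving 5 points to the margin.

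Items 2 and 3 are inferred by back-calculation, so the authors should check them against their original computation before printing. The cost is wording only, with no operational change. The stated power becomes slightly less favourable.

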### Setting and recruitment

A total of 186 subjects will participate in the study and will be recruited from 9 participating research centers (the hospital). Prior to recruitment, the investigator will carefully study the past condition, including but not limited to disease diagnosis and previous dialysis status of each participant. Researchers will fully consider the compliance of the participants within 24 weeks based on asking the participants. Informed consent forms (ICFs) will be obtained before collecting any participant data and participant information. After the participants sign the ICFs, the investigators will also sign the ICFs and record the informed consent process in the medical records. Hemodialysis participants eligible for inclusion in the trial will receive intravenous infusion (100mg total) of iron sucrose for 2 weeks after initial screening. If they still meet the inclusion criteria, they will be formally enrolled and started on medication. The treatment follow-up period of each participant is 24 weeks; the follow-up point of the screening and treatment period are shown in Fig. 2.

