#### Exclusion criteria

Participants who meet any of the following criteria will not be eligible to participate in this clinical trial:
Iron allergy, allergic history, or intolerance to test drugsHaving erythrocyte aplastic anemia, other hematopoietic and hemolytic diseasesAcute or chronic bleedingSerum albumin < 35g/LHypersensitive C-reactive protein >10 mg/LSevere secondary hyperparathyroidism (iPTH ≥800 pg/mL)Severe cardiac dysfunction (NYHA score > 3) and poor control of hypertension (systolic blood pressure ≥ 180 mmHg or diastolic blood pressure ≥ 100 mmHg)Severe liver disease (ALT, AST, and TBIL ≥ 2 times the upper limit of normal) or hepatitis B surface antigen positive, or hepatitis C antibody positiveMalignant tumorSevere bacterial or viral infection that occurred in the last 1 month, prior to signing the consentHistory of blood transfusion in the last 1 monthAdmitted to a hospital or planned a kidney transplant within the next 24 weeksPregnant or breastfeeding womanLife expectancy less than 12 monthsParticipating or has participated in clinical trials of other drugs within the last 3 monthsGastric or duodenal ulcers or ulcerative colitisHistory of chronic alcohol abuse, substance abuse. The presence of conditions that the investigator believes may affect participants’ compliance or test results

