### Intervention

#### Experimental group

Iron polysaccharide complex (150mg) will be taken orally, 2 capsules per day, for 24 weeks. Participants will be treated with biosimilar epoetin (no need to dilute) intravenously with a single dose of 10,000U once a week during the maintenance period. At the same time, biosimilar epoetin dosage will be adjusted according to the measured hemoglobin concentration, as follows [7].
Discontinue biosimilar epoetin if Hb ≥ 130 g/L. Hb levels will be checked once every 2 weeks. If the Hb level drops to 110–130 g/L, the original biosimilar epoetin dose will be reduced by 25% or extended to once in 10 days for continuation.If Hb < 110 g/L, TSAT, and SF are met, biosimilar epoetin will be administered as a single dose of 10,000U at least three times, every 2 weeks. Also, the Hb values of participants will be evaluated once every 2 weeks. The maximum dose of biosimilar epoetin will be 10,000U twice a week. If TSAT and SF fail to meet the standard, the iron deficiency will be corrected first, and the biosimilar epoetin treatment regimen will be adjusted once TSAT and SF are within the desired range.

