#### Control group

One hundred milligrams of iron sucrose injection dissolved in 100 mL 0.9% sodium chloride solution will be intravenously administered at the end of dialysis once every 2 weeks for 24 weeks. During this period, participants will continue to receive intravenous biosimilar epoetin treatment in the same way as the experimental group. For the first intravenous infusion of iron sucrose injection, a small test dose will be performed. The test method refers to the drug instructions of iron sucrose injection, which are as follows.
Dosage: 1–2.5 mL (20–50 mg iron content) for adults. Children should be given 1 mL (iron content 20 mg) each time with body weight > 14 kg and given half of the daily dose (body weight kg × 1.5 mg/kg) each time with body weight < 14 kgCaution: cardiopulmonary resuscitation equipment should be available during the test. If no adverse reactions occur after 15 min of administration, the remaining administration can be continued

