### Withdrawal and drop-out

Participants can withdraw from the clinical trial at any time for any reason without prejudice to the investigator’s right to treat their disease. After fully considering the benefit of the participants, the investigator has the right to request the participants to withdraw for any reason, such as the occurrence of concomitant disease, adverse events [13], or treatment failure. The ethics committee reserves the right to request withdrawal of the participants for program violation, administrative reasons, or other valid and ethical reasons. All participants withdrawing from the clinical trial must complete a final trial evaluation. And the reason for withdrawal will be stated in the eCRF with all other appropriate and valuable information. Specific discontinuation and exit criteria are listed below.

Discontinuation criteria:
Participants not having used the drug even onceWithout any test records or follow-up data, no safety and efficacy data recordsAffecting the trial evaluation by using prohibited treatments and drugs in the protocol within the next 24 weeksOther serious breaches of the scheme (participants with serious non-compliance to discharge criteria)

Exit criteria:
Exit requested by the participantsRecurring intolerable adverse reactionsSF ≤ 200 μg/L or TSAT ≤ 20% within 2 consecutive monthsHb concentration < 90 g/L or > 130g/L within 2 consecutive monthsPoor compliance, failure to comply to protocol thus affecting efficacyStudy observations could not be continued due to unforeseen circumstances occurring during the test

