#### Data set category

Intention-to-treat (ITT): No one was excluded from the main analysis set after randomizationPer-protocol set (PPS): Good compliance case data that meets the main inclusion and exclusion criteria without affecting the main curative effects of prohibiting drugs within the next 24 weeksSafety set (SS): Case data involving usage of the investigational drug product at least once, including safety evaluation

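### The poor-compliance exit rule falls mainly on the oral arm and can remove week-12 TSAT from the ITT analysis, so both analysis sets may lean toward non-inferiority

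*Protocol article*

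**What the plan says.** All references are to the protocol article.

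- **Before randomisation.** Setting and recruitment: "Researchers will fully consider the compliance of the participants within 24 weeks based on asking the participants". The last exclusion criterion adds "The presence of conditions that the investigator believes may affect participants’ compliance or test results".
- **After randomisation.** The exit criteria under Withdrawal and drop-out list poor compliance, or failure to follow the protocol, where this affects efficacy. No dose count, percentage or time window is given. The same section requires that "All participants withdrawing from the clinical trial must complete a final trial evaluation". It does not say that TSAT is still drawn at week 12.
- **Administration.** The capsules "will be taken orally, 2 capsules per day, for 24 weeks". Iron sucrose is "intravenously administered at the end of dialysis once every 2 weeks for 24 weeks". Participants dialyse three times a week (Inclusion criteria).
- **Analysis sets.** Data set category keeps every randomised participant in the ITT set, which it calls the main set. The per-protocol set is "Good compliance case data that meets the main inclusion and exclusion criteria", also without prohibited drugs.
- **Endpoint and test.** The primary endpoint is TSAT at week 12. Continuous outcomes are compared by Student's t-test. The Discussion states the non-inferiority hypothesis, and the Trial design section states that the trial is open.

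**The concern.** Missed doses are one of the main ways in which a capsule prescribed for daily use could do worse than iron given by staff at dialysis. In a non-inferiority trial this belongs to the treatment effect under study. A rule that takes poor compliers out after randomisation removes the participants in whom the oral arm is expected to do worst, and it is applied by people who know the assignment.

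The usual safeguard is to compare ITT with per-protocol results. It is weakened here because both sets may carry the same selection: the per-protocol set by definition, and the ITT set to the extent that early exits leave no week-12 TSAT. Agreement between them would then give false reassurance. The Discussion intends the result to support an alternative treatment for hemodialysis patients generally, and for that claim the effect of prescribing capsules matters, including in those who take them badly.

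**Working it through.** **1. Which filters can bias the comparison**

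| Filter | Timing | Effect |
|---|---|---|
| Asking candidates about compliance; investigator-judged exclusion | Before randomisation, both arms | Narrows the population; no between-arm bias |
| Exit for poor compliance | After randomisation, no threshold | Can bias if exits differ by arm and relate to TSAT |
| Good-compliance per-protocol set | After randomisation | Same mechanism, by definition |

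**2. Why the exits should be unequal.** Infusions every 2 weeks make about 12/2 = 6 control doses by week 12, each given at a session the patient already attends. Capsules are due every day, and with three sessions a week at least 7 - 3 = 4 days a week fall away from the unit.

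**3. Reproducing the plan's sample size.** The Sample size section gives a "non-inferiority threshold of 7 (%) and a variance of 11 (%) for the positive control group", a predicted 2-point difference, one-sided 2.5% and 80% power. The figure of 11 works only as an SD.

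- Normal approximation: n per arm = 2 × (1.960 + 0.842)² × 11² / (7 - 2)² = 76.
- Noncentral t: n = 77, power 80.0%. The stated 77 per arm reproduces.
- Read as a true variance (SD = √11), it would give only 7 per arm.

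**4. Size of the shift.** Let f be the share of the oral arm that exits before week 12 without a week-12 value, and D the amount by which their TSAT would fall below that of the remaining oral participants.

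- Oral mean in all randomised = (1 - f)μ + f(μ - D) = μ - fD.
- Oral mean after removal = μ, so the observed deficit shrinks by fD.
- If a share g of controls also exits with deficit D′, the net shift is fD - gD′. The illustration sets g = 0.

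Neither f nor D is in the documents. The assumed range is f = 10-20% and D = 5-10 TSAT points.

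**5. Effect on the false non-inferiority rate.** Set the true all-randomised deficit at the margin, 7 points, where the rate should be 2.5%. The noncentrality of the t-test is then fD / SE, with SE = 11 × √(1/n₁ + 1/n₂). At 77 per arm, SE = 11 × √(2/77) = 1.773. With the oral arm reduced to 77(1 - f), SE is 1.821, 1.849 and 1.880 in the three rows.

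| f | D | fD | Analysed deficit | Rate, 77 v 77 | Oral n left | Rate, reduced arm |
|---|---|---|---|---|---|---|
| 10% | 5 | 0.5 | 6.5 | 4.7% | 69.3 | 4.6% |
| 15% | 8 | 1.2 | 5.8 | 9.9% | 65.5 | 9.4% |
| 20% | 10 | 2.0 | 5.0 | 20.1% | 61.6 | 18.3% |

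A milder case, f = 5% and D = 5, gives 3.4% either way. If the off-treatment week-12 values were measured and analysed as randomised, fD would return to the oral mean and the rate would stay at 2.5%.

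**The case against.** The strongest reply is that the ITT set excludes nobody. The article never says that TSAT is omitted from the final evaluation or that later collection is barred. The assessment schedule figure is not available here, and handling of missing values commonly sits in a statistical analysis plan that is not shown. Anyone who exits after week 12 already has the primary value. Much of this stands: the effect on ITT is a risk created by early exits, not a stated exclusion. What remains is that the text secures a final evaluation and no week-12 sample. An analysis plan can model a missing value but cannot recover a sample never drawn. An exit value is also no clean substitute, because it lies nearer the run-in iron sucrose and may overstate a non-taker's week-12 TSAT.

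Other objections also limit the point:

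- **Both arms can fail to comply.** Control participants can miss or refuse infusions, and visits, prohibited drugs and the epoetin regimen apply to everyone. A reader might infer that only the oral arm can be affected; the documents support no more than mainly.
- **Application is discretionary.** The investigator has a right to request withdrawal and the criterion has no threshold, so its frequency is unknown.
- **The assumed range may be high.** With 1:1 allocation, 20% of the oral arm is 10% of all randomised, half the planned 20% drop-out, and it would have to occur by week 12. Participants also enter iron-replete, so the deficit at 12 weeks is uncertain.
- **Overlap.** A separate exit criterion for persistently low ferritin or TSAT would already take out some non-takers, so the added effect of this rule is smaller than the shift computed above.
- **A compliance-based per-protocol set is conventional**, and nothing says that it alone decides non-inferiority.

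**Conclusion.** The concern holds in a limited form and should be fixed. An open-label exit rule for poor compliance, without a threshold and falling mainly on the arm with the daily oral regimen, can leave week-12 TSAT missing from the ITT analysis, while the per-protocol set applies a further compliance filter. If oral non-takers have lower TSAT, both analyses lean toward non-inferiority. The direction follows from the text and that one condition.

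The size does not follow from the documents. The rise from 2.5% to about 5-18% (about 5-20% at 77 per arm) rests wholly on the assumed exit rates and TSAT deficits, no compliance exits among controls, and an analysis of observed values only.

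Three stronger readings are not supported:

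- That the entry screen biases the comparison. It acts before randomisation on both arms and affects only generalisability.
- That the trial as a whole compares iron sucrose with adherent capsule takers. This describes the per-protocol set, and the ITT set only so far as early exits lack the endpoint.
- That true power falls short of the planned 80% for this reason. That would require the predicted 2-point difference to mean the deficit among adherent takers, and the Sample size section makes no such restriction.

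**What to change.** 1. **Withdrawal and drop-out.** Record poor compliance as a protocol deviation and not as a reason to end follow-up. Whether the participant continues the assigned iron is a separate clinical matter that this change does not touch.
2. **Follow-up.** Keep these participants on the visit schedule and measure week-12 TSAT in everyone randomised, including those off treatment.
3. **Data set category.** State that the primary non-inferiority analysis is ITT, as randomised, using those values, and that the compliance-restricted per-protocol set is supportive and cannot establish non-inferiority alone.

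The cost is amendment wording plus a few retained visits and blood samples, from patients who already attend dialysis three times a week. The oral arm's result may look less favourable, but it would then answer the question the trial poses.
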